| Control group                                         | Success will be compared to historical success achieved without the use of SML.                                                                                                                                                                                                                                                                                                                                                                                                                                                                                                                                                                                                                                                                                                                                                                                                                                                                                                                                                                                                                                                                                                                                                                                                                                                                                                                                                                                                                                                                                                                           |

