| Primary outcomes                                      | 1. Feasibility : Acceptance of and satisfaction with SM recruitment method among USC Norris study team members and Twitter users in LA County, number of cancer trials eligible to be enrolled in study, number of cancer disease types and studies that can be monitored for on Twitter simultaneously by the SC CTSI study team, time and effort it takes the SC CTSI and USC Norris team members to respond to the resulting inquiries and decide whether or not to bring the patient in for screening, eligibility rate of prospective participants, demographic and ethnic diversity rate of those who consented/enrolled, social media message click rate, website contact form usage rate.
2. Impact : Monthly observed recruitment rate vs. monthly projected accrual target by trial disease group compared to historic data. Effect size estimate of the number of people to enroll cancer trials as a result of targeted social media listening and recruitment (SML) via Twitter.                                                                                                                                                                                                                                                                                                                                                                                                                                                                                                                                                                                            |

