| Analysis plan                                         | 1. Feasibility will be assessed by describing the acceptance of and satisfaction with SM recruitment method among USC Norris study team members and Twitter users in LA County and by describing the proportion of eligible cancer trials to be enrolled in the study, cancer disease types and studies that can be monitored for on Twitter at a time, time and effort it takes the SC CTSI and USC Norris team members to respond to the resulting inquiries and decide whether or not to bring the patient in for screening, eligible participants that can be enrolled, demographic and ethnic diversity of participants, and staffing required to monitor eligible studies.
2. Impact : The efficacy aim will be determined comparing monthly actual vs. projected rate of recruitment for the trial disease groups (i.e., non-small cell lung cancer, colon cancer, breast cancer, prostate cancer, kidney cancer, lymphoma) using generalized estimating equations, accounting for intra-disease random effects and trends across the 12 months (9 months exposure per trial). These results will then be put into context of the historic recruitment for these diseases at the center. We will also explore patient characteristics between the two groups to examine where differences might lie. Exploratory variables will also include the number of open trials and amendments to the trials and changes to status. Effect size estimate of the number of people to enroll cancer trials as a result of targeted social media listening and recruitment (SML) via Twitter. |

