### *3.3.7 Data analysis*

Feasibility will be assessed by describing the acceptance of and satisfaction with the SM recruitment method among USC Norris study team members and Twitter users in LA County, number of cancer trials eligible to be enrolled in study at the time of this study (current estimate of 84 is based on latest data from USC Norris), number of cancer disease types and studies that can be monitored for on Twitter simultaneously by the SC CTSI study team, time and effort it takes the SC CTSI and USC Norris team members to respond to the

resulting inquiries and decide whether or not to bring the patient in for screening, eligibility rate of prospective participants, demographic and ethnic diversity rate of those who consented/enrolled, social media message click rate, website contact form usage rate, social media message click rate, website contact form usage rate. **Table 3** lists all primary outcomes measures we intend to use.

To facilitate qualitative data analysis, we will develop an initial code list based on the interview guide. The code list will be modified throughout the coding process. Each coded transcript will be discussed line by line until the coding team came (Drs. [name] and [name]) to an agreement about code definitions and how they should be applied. Important themes will be summarized and used to understand satisfaction with SM-based recruitment strategies for cancer-related clinical trials.

Count outcomes will be presented as median and interquartile range, nominal outcomes will be presented as N (%). We will explore patient and study characteristics between the two cohorts to examine where differences might lie by including them as potential covariates in the models. Comparisons of the before- and after time periods will be made using generalized estimating equations for appropriate outcome type (Poisson, means, prevalence) accounting for type of cancer.

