The **efficacy** aim will be determined comparing monthly actual vs. projected rate of recruitment for the trial disease groups (i.e., non-small cell lung cancer, colon cancer, breast cancer, prostate cancer, kidney cancer, lymphoma) and compared to historic data by trial disease group using generalized estimating equations, accounting for intra-disease random effects and trends across the 12 months (9 months exposure per trial). Statistical analyses of primary aims will be carried out by [name] [name], an SC CTSI biostatistician. Analyses will be performed in SPSS v24 [41]. As this is a pilot study, p-values are of limited use to determine group differences, so we will focus on observed effect sizes (Cohen's D, Relative Risk).

**Table 3** lists all primary outcomes measures we intend to use. In addition, **Appendix 5 (data dictionary)** provides the full set of metrics we will use to assess the success of the intervention, which includes additional success metrics such as number of contacts solicited, number of contacts who acknowledge the solicitation, number of social media contact/recruitment messages sent, day/time of contact, day/time of response.

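### The efficacy aim is given two analyses that treat historic accrual differently, and actual versus projected accrual alone does not estimate the effect of social media listening (SML)

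*Protocol*

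**What the plan says.** The protocol describes the impact (efficacy) analysis in several places, and they do not agree on what history is for.

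**History outside the comparison, or absent**
- Synopsis, Analysis plan row: "The efficacy aim will be determined comparing monthly actual vs. projected rate of recruitment for the trial disease groups", by GEE. The next sentence adds "These results will then be put into context of the historic recruitment for these diseases at the center".
- Section 3.3.1, last paragraph: impact is the monthly observed rate against the monthly projected target. History is not mentioned.

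**History as comparator**
- Synopsis, Control group row: "Success will be compared to historical success achieved without the use of SML".
- Synopsis, Primary outcomes row: "Monthly observed recruitment rate vs. monthly projected accrual target by trial disease group compared to historic data".
- Section 2.2, research question II: the enrolment rate under SML is to be compared with historic recruitment, measured as actual versus projected accrual.
- Section 3.3.1: an interrupted time series with a before and an after period.
- Section 3.3.7: "Comparisons of the before- and after time periods will be made using generalized estimating equations for appropriate outcome type". The efficacy paragraph keeps actual versus projected and continues "and compared to historic data by trial disease group using generalized estimating equations, accounting for intra-disease random effects and trends across the 12 months".

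Section 3.3.7 also says that, as this is a pilot, p-values are of limited use and observed effect sizes are the focus. Table 4 says the estimated effect size will support a larger grant proposal.

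**The concern.** In one description history sits after and outside the model. In the other it is inside it. The two contrasts need not have the same value when SML does nothing.

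An accrual target is what each trial team hoped for. It does not estimate what would have accrued without SML, so actual/projected taken alone mixes any SML effect with how ambitious the targets were. Research question II asks how enrolment under SML compares with historic recruitment, and that needs a before/after contrast.

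The effect size is what this pilot is meant to deliver and carry into the next application. If its definition depends on which section the analyst follows, the figure carried forward is not well defined.

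**Working it through.** The protocol gives no planned ratio, power or sample size for the impact aim, so there is no stated figure to reproduce. The check is the value each contrast would take with no SML effect.

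**Inputs**
- Trials: 84, stated in section 3.3.3 to meet the inclusion criteria.
- Minimum target per trial: 1 per month and 12 per year (section 3.3.3).
- Accrual: Appendix 2, interventional therapeutic rows, six sites pooled.
  - 2016: 33 + 49 + 64 + 52 + 7 + 9 = 214
  - 2017 to 27 June: 17 + 21 + 33 + 21 + 4 + 4 = 100, in 178 days = 5.85 months
  - 2012-2016: 330 + 280 + 305 + 282 + 214 = 1,411, in 60 months
- Historic window: section 3.3.3 refers to the past five years.

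**Monthly accrual**
- 2016: 214 / 12 = 17.8
- 2017: 100 / 5.85 = 17.1
- 2012-2016: 1,411 / 60 = 23.5

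**Contrast 1: actual / projected, no SML effect**

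Projected accrual is at least 84 × 1 = 84 per month, so each ratio is an upper bound.
- 2017 rate: 17.1 / 84 = 0.20
- 2016 rate: 17.8 / 84 = 0.21
- 2012-2016 mean: 23.5 / 84 = 0.28
- All-interventional rows, same order: 0.22, 0.23, 0.34

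Actual targets are not given. Assuming that only some trials carry the minimum target and that they bring all the accrual, the 2016 rate gives 17.8 / 60 = 0.30 for 60 trials and 17.8 / 30 = 0.59 for 30.

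**Contrast 2: after / before, no SML effect**

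Using the 2017 rate as the after period, since it predates SML:
- Against 2016: 17.1 / 17.8 = 0.96
- Against the 2012-2016 mean: 17.1 / 23.5 = 0.73
- All-interventional rows: 0.95 and 0.64

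By disease group, against the 2012-2016 mean:

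| Site | 2017 per month | 2012-2016 per month | Ratio |
|---|---|---|---|
| Lung | 2.91 | 2.23 | 1.30 |
| Colon | 3.59 | 5.08 | 0.71 |
| Breast | 5.64 | 7.68 | 0.73 |
| Prostate | 3.59 | 5.25 | 0.68 |
| Kidney | 0.68 | 2.48 | 0.28 |
| Lymphoma | 0.68 | 0.78 | 0.87 |

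The before/after ratio is therefore near 1 with a recent baseline, or if the trend is modelled. It is not near 1 against an unadjusted five-year mean. Even so, the two contrasts differ several-fold under no effect: 0.20 against 0.73 to 0.96, pooled, at the 2017 rate with the 84-trial minimum.

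**The case against.** The case on the other side has real force on several points.

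- **Section 3.3.7 does not replace the target with history.** It opens with the same actual-versus-projected contrast and adds history, and the objectives and primary outcome use the same compound measure. It can be read as two comparisons or as a change in actual/projected. This stands: section 3.3.7 does not fix a single estimand either.
- **The synopsis as a whole does not reduce history to context.** Only its analysis-plan row does. This also stands, and it means that row conflicts with its own synopsis.
- **A reader might infer that the synopsis GEE uses SML months only.** The row does not say so. It refers to trends over 12 months with 9 months of exposure, as section 3.3.7 does, and to two groups. What it does say is that history comes in after the results.
- **A reader might infer that the study would report failure whether or not SML adds patients.** The documents do not support this. No success threshold is set, effect sizes rather than p-values are the focus, and a low ratio would be read beside history. The plan also estimates enrolment resulting from SML, using tagged messages and tracking sheets (sections 3.3.4 and 3.3.5, Table 4).
- **The 0.2 is a bound that depends on the count of 84.** Whole-site accrual in 2016 was 7 for kidney and 9 for lymphoma, below the minimum of 12 a year for a single trial. The count or the targets may themselves be in doubt. Appendix 2 also counts lung, not only non-small cell lung cancer.
- **Model detail can sit in a statistical analysis plan.** That is true of covariance structure and similar terms. Here the protocol states the comparison itself more than once, in forms that differ.

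**Conclusion.** The inconsistency is in the text. The synopsis analysis-plan row and the last paragraph of section 3.3.1 leave history out of the comparison. The synopsis control and primary-outcome rows, research question II, the stated design and section 3.3.7 bring it in. Actual/projected alone does not estimate the SML effect.

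If all 84 trials carry at least the minimum target and the six sites are pooled, the no-effect ratio is at most 0.20 to 0.21 at 2016-2017 accrual. It is 0.28 at the 2012-2016 mean, and 0.30 or 0.59 if only 60 or 30 trials carry such targets (assumed). None of these is near 1.

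A reader might also infer that putting history in the model gives a no-effect value of 1 automatically. It does not: 2017 gives 0.96 against 2016, but 0.73 against the five-year mean and 0.28 to 1.30 by disease. The choice of window and the handling of trend matter as much as the choice of comparator.

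**What to change.** Describe the impact analysis in the same words in the synopsis (Primary outcomes and Analysis plan rows), the last paragraph of section 3.3.1, and section 3.3.7:

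1. The impact effect estimate is the SML versus pre-SML contrast within disease group, from one model containing both periods.
2. It is expressed as the accrual rate ratio or, where targets exist for both periods, as the change in actual/projected.
3. The historic window is stated and the time trend is modelled.
4. SML-period actual versus projected accrual on its own is reported descriptively, alongside the planned count of Twitter-attributed enrollees.

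The cost is wording and slightly more modelling of historic accrual that the protocol already plans to use. Appendix 2 prints annual totals only, so monthly counts would be needed for the pre-SML period. The monthly comparison with history already implies them.

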# 1. PURPOSE OF THE STUDY

## 1.1 Name of intervention

This study will examine the feasibility and gain preliminary data on the impact of targeted social media listening (SML) as a tool for enhancing recruitment to cancer trials (non-small cell lung cancer, colon cancer, breast cancer, prostate cancer, kidney cancer, lymphoma) among Twitter users in LA County.

## 1.2 Intended use of the intervention

We will use the Symplur Signals database to identify in real time people in California who mention one or more of the pre-selected cancer topics (non-small cell lung cancer, colon cancer, breast cancer, prostate cancer, kidney cancer, lymphoma) on Twitter. Symplur Signals is a healthcare SM analytics platform that maintains a database of curated disease- and health-related Twitter conversations and user data, updated daily and easily sortable by SM user type (patient, physician, health care organization), location and time zone, language, disease/health interests, message content, sentiment, and SM influence. We will use the data to identify users on Twitter in LA County who mention specific disease/health-related keywords and contact them to recruit them into clinical trials. Those individuals are then targeted for recruitment using a combination of SM and traditional methods.

## 1.3 Study objectives

1.3.1 Examine the feasibility (acceptance among USC Norris study team members and Twitter users in LA County) of targeted social media listening (SML) via Twitter as a tool for enhancing recruitment to cancer trials.

1.3.2 Gain preliminary data on the impact (i.e., numbers recruited versus projected accrual compared to historic recruitment) of targeted social media listening (SML) as a tool for enhancing recruitment to cancer trials among Twitter users in LA County. Estimate the effect size of the number of people enrolled associated with the use of targeted social media listening (SML) via Twitter as a tool for enhancing recruitment to cancer trials.

## 1.4 Anticipated duration of the clinical investigation

We estimate 14 months to complete the proposed study including the data analysis and dissemination. The intervention exposure time is 9 months per enrolled trial. Disease categories will be rolled consecutively, one every two weeks in the first quarter. Order will be randomized.

## 2. BACKGROUND

### 2.1 Problem the study addresses

In 2012, the Institute of Medicine recognized the seriousness of the clinical trial participation problem [1] and released a report that identified numerous barriers, including the lack of awareness among patients that clinical trials are available. Identifying and recruiting the full complement of participants into a trial is challenging and costly. Nearly a third of the time and resources dedicated to clinical trials is spent on study participant recruitment [2]. Despite this substantial investment, many trials fail to meet enrollment targets. Authors of randomized trials have reported that nearly 60% of them had either failed to meet their recruitment target or required an extended recruitment period to do so [3-8]. Therefore, we propose to provide evidence for the feasibility of a new clinical trial recruitment solutions to identify and recruit participants into cancer clinical trials at USC Norris.

### 2.2 Rationale

Studies suggest that social media (SM) such as Twitter and Facebook serve as a useful tool to recruit research participants in a variety of disease and health contexts. SM are widely accessible Web-based and mobile technologies that allow users to view, create and share information online and to participate in social networking [9]. The SM platform Twitter, for example, was successfully used to recruit cancer patients [10], young women into nutrition research studies [11], and adolescents with type 1 diabetes and their parents [12]. A recent scoping review concluded that SM can be more efficient than traditional recruitment methods for hard-to-reach populations and observational studies [13]. Paid advertisement (ads) on Facebook have shown to lead to higher enrolment rates than messages on Twitter, where ads about clinical trials and recruitment are not permitted [13]. However, in previous studies, SM were used as unidirectional communication tools to distribute messages from academic institutions to communities that did not take into account community-generated user data from SM to identify prospective study participants who have expressed interest in specific disease/health topics and to inform and guide recruitment strategies. Many research institutions use SM to distribute information about biomedical research and ongoing research activities to the public but most messages are purely informational and designed to increase transparency about activities. We propose to develop and evaluate a complementary SM monitoring approach that allows research institutions to utilize community-generated SM data from Twitter in order to identify prospective participants based on health interests and disease topics they mention on Twitter and to recruit them into clinical trials.

SM monitoring describes the process of gaining insights from SM community-generated data such as users' messages, profile descriptions, and locations. The proposed SM intervention is based on the dissonance-based health behavior model [14] and hypocrisy paradigm [15,16] that was found to be the most commonly applied research paradigm and was most effective at inciting change across a range of health behaviors [17]. After people express public support for something (e.g., a disease type, clinical trial), they become motivated to act in a way that is consistent with their professed beliefs. If a person says positive things about a clinical trial and then declines to participate in a clinical trial, that creates cognitive dissonance, which may be uncomfortable. To reduce the dissonance, people who have said positive things about clinical trials may be more likely to enroll in a clinical trial (or at least express some interest in enrolling).

Previous studies have examined the use of SM monitoring data via Twitter and other SM in different contexts such as public health surveillance [e.g., 18-20]; public health safety and

emergency response operations [e.g., 21,22]; tobacco regulatory sciences [e.g., 23-25]; and monitoring pharmaceutical products, potential drug interactions and adverse events [e.g., 26-29]. The feasibility of using SM monitoring in clinical research is supported by limited reports from the pharmaceutical industry [30]. However, sponsors have reported that the lack of experienced vendors, Clinical Research Offices and internal teams to conduct SM monitoring to inform clinical research is the main barrier to the adoption of SM monitoring [30].

**Focus on Twitter and cancer trials:** We propose to focus on the SM platform Twitter and cancer clinical trials for the following reasons: Previous studies provide evidence of “a rapidly evolving network of cancer patients engaged in information exchange via Twitter” [31, 32] that can serve as a powerful and important tool in implementing and disseminating critical messages to the community in real-time” [31]. The increasing use of Twitter among members of the cancer disease community is evidenced by the growing use of specific hashtags [32-37]. A hashtag is a user-generated word or phrase preceded by a hash or pound sign (#) and used to identify messages on a specific topic on Twitter and other SM platforms. For example, rather than #breastcancer or #bcancer, the most widely recognized hashtag for breast cancer is currently #BCSM (Breast Cancer Social Media). Furthermore, Twitter is a public social network which makes it an ideal candidate to test the proposed research idea. By default, basic Twitter account information such as the profile name, description and location are public unless a user decides to opt out and make his/her account private. SM such as Twitter are also a “rich and promising avenue for exploring how patients conceptualize and communicate about their specific health issues” [38]. A study on lung cancer-related Twitter messages, for example, found that these messages focused on support, prevention, and clinical trials, and were predominantly authored by individuals [39]. Therefore, we hypothesize that the Twitter network can be used for precision recruitment to identify, engage and recruit prospective study participants, and that previously reported recruitment rates via Twitter can be increased through SM monitoring.

Research questions we aim to answer with this study:

**I. How feasible is the application of SML to enhance recruitment for clinical trials among Twitter users in LA County? This will be measured as follows:**

- a. How many PI's are willing to participate in this study?
- b. How many cancer trials that meet the eligibility criteria can be enrolled?
- c. What are reasons for not enrolling eligible trials?
- d. How many trials and disease categories can be monitored at a time? Monitoring means that the SC CTSI study team listen to conversations on Twitter that mention the select disease terms (i.e., non-small cell lung cancer, colon cancer, breast cancer, prostate cancer, kidney cancer, lymphoma) to identify potential study participants in LA County.
- e. How does the intervention affect the enrolled study and study staff?
- f. How much time and efforts does it take to respond to the resulting inquiries and decide whether or not to bring the patient in for screening?
- g. How does the intervention affect prospective participants' satisfaction?
- h. How many prospective participants are eligible?
- i. How diverse are enrolled participants? (demographic and ethnic diversity)

